**Figure 2 F2:**
[figure not shown]
Electromyography equipment used in this study.

**Figure 3 F3:**
[figure not shown]
Electrodes placement.

### Analysis of sEMG data

The average data will be expressed in RMS (Root Mean Square) which qualitatively expresses the record of electrical activity of muscles under study 
[27].

### Protocol for electromyographic examination

It will be used a mandibular force transducer (EMG System of Brazil Ltda, Sao Jose dos Campos, SP) [Figure 
4 to record the maximum bite force, which consists of a mechanical device with sensors that record material deformations during the bite. This deformation is converted into kgf or Newton by means of EMGLab V1.1 software (EMG System of Brazil Ltda). In order to measure the mouth opening amplitude, it will be adopted a mandibular goniometer (EMG System do Brazil Ltda, Sao Jose dos Campos, SP) [Figure 
5. The electromyographic recordings will be performed in all phases of the study, described below, in the rest position, isometric position, bite force, using a transducer, and opening/closing with the aid of the mandibular goniometer. Each EMG recording will last ten seconds with an interval of one minute and will be repeated three times at the same appointment 
[28].

**Figure 4 F4:**
[figure not shown]
Mandibular force transducer equipment used in this study.

**Figure 5 F5:**
[figure not shown]
Mandibular goniomenter equipment used in this study.

### Phases of electromyographic exam

The sEMG, referring to the masseter, temporallis, supra-hyoid, bite force and range of mandibular opening shall be provided in four distinct phases. Phase 1- initial data collection (Groups 1 to 5); Phase 2- treated groups (Groups 1 to 5) after 1 week of electrical stimulation with or without laser and LED therapy; Phase 3-treated groups (Groups 1 to 5) after 4 week of electrical stimulation with or without laser and LED therapy and Phase 4-treated groups (Groups 1 to 5) after 8 weeks after the last electrical stimulation with or without laser and LED therapy.

Data obtained will be compared among each group to verify the effectiveness of the proposed therapies to improve the masticatory muscle activity in patients with CP.

### Protocol for laser and LED therapy

After the evaluation and diagnosis, patients will be randomly divided into 5 groups (n = 10). Groups 2 to 5 will be treated with lasertherapy or LED theraphy, combined or not with electricalstimulation twice a week for eight consecutive weeks, following the protocol of 
[29].

The craniofacial complex will be irradiated in 12 areas, being 1. posterior region of the temporomandibular joint (TMJ) with open mouth, reaching the auriculo temporal nerve; 2. area prior to the sigmoid notch, insertion area of the lateral pterygoid muscle (upper beam) at the neck of the condyle and disk; 3. articular interface between condyle and fossa with open mouth; 4. angle of the jaw; 5. anterior temporal muscle; 6. middle portion of the temporal muscle; 7. posterior portion of the temporal muscle; 8. upper, middle and bottom of the sternocleidomastoid muscle; 9. anterior portion of occipitofrontal muscle; 10. posterior portion of the occipitofrontal muscle; 11. superficial portion of the masseter; and 12. supra-hyoid muscles. In groups 2 and 4, these anatomical structures will be irradiated with a laser diode of gallium arsenide and aluminum-GaAlAs (TWIN Laser, Optics brand MM), emitting at a wavelength of 660 nm, with a constant power 40 mW, and a maximum beam diameter of 0.38 cm^2^. Groups 3 and 5 will be irradiated with a light emitting diode (LED), emitting a wavelength band of 630 ± 5 nm, with a constant power 40 mW, and the maximum laser beam diameter of 0.38 cm^2^. Both will be operated in continuous mode and should be used in contact with the target tissue, providing an irradiance or intensity of 0.40 mW/cm^2^. The incidence of fluency range for each point of application will be of 12.0 J/cm^2^, and the irradiation time of 30 seconds for each predetermined point.

### Protocol for neuromuscular electrical stimulation (NMES)

NMES is a noninvasive technique, without systemic effects, is not addictive and has no undesirable side effects. This technique consists on the application of mild electrical stimulation through electrodes placed on the surface of muscles. It induces action potentials in motor nerve, causing activation of motor units 
[30]. Effects such as strengthening the stimulated muscles, facilitation of voluntary motor control 
[31] and decreased spasticity have been reported.

Neuromuscular electrical stimulation (Neurodyn III) equipment will be used. In this study, a protocol will be applied based on Nunes 
[32] recommendations, which are sessions of 30 minutes (divided between the superficial portion of masseter, the anterior portion of temporalis muscle and supra-hyoid, according to the electromyogram diagnosis), 2 times per week for 8 weeks compatible with a total of NMES 16 sessions in patients of Groups 1, 4 and 5. After 8 weeks of NMES training, both neural and muscular adaptations mediate the strength improvement .

### Protocol for polysomnography

A full-night PSG 
[33] will be performed prior and after all therapies, using a digital system (Embla, A10 version 3.1.2 Flaga, Hs. Medical Devices, Iceland) at the Sleep Laboratory of University of Nove de Julho. All recording sensors will be attached to the patient in a non-invasive manner using tape or elastic bands. The following physiological variables will be monitored simultaneously and continuously: four channels for the electroencephalogram (EEG) (C3-A2, C4-A1, O1-A2, O2-A1), two channels for the electrooculogram (EOG) (EOG-Left-A2, EOG-Right-A1), four channels for the surface electromyogram (muscles of the submentonian region, anterior tibialis muscle, masseter region and seventh intercostal space), one channel for an electrocardiogram (derivation V1 modified), airflow detection via two channels through a thermocouple (one channel) and nasal pressure (one channel), respiratory effort of the thorax (one channel) and the abdomen (one channel) via x-trace belts, snoring (one channel) and body position (one channel) via EMBLA sensors, and arterial oxygen saturation (SaO2) and pulse rate via an EMBLA oximeter. All PSGs will be performed and sleep stages visually scored according to standardized criteria for investigating sleep. EEG arousals, sleep-related respiratory events and leg movements will be scored in accordance with the criteria established by the American Academy of Sleep Medicine Manual for Scoring Sleep and Associated Events 
[34]. The patients will be instructed to remain as relaxed as possible and sleep naturally, as if at home. All signals will be recorded continuously. Throughout the night, all the subjects will be monitored by a technician experienced in polysomnography 
[33].

### Quality control

In order to ensure data quality, dentists in charge of EMG exam, as well as the speech-therapist in charge of oral movements and sleep technician in charge of the data acquisition of polysomnography will receive specific training. Periodic external monitoring will be performed to verify the adequate polysomnnographic examination. The results of the preoperative and postoperative exams will be analysed by blinded evaluators.

### Statistical analysis

Data will be presented as means ± standard deviation, when applicable. For comparison of continuous variables prior and after polysomnography and specifics therapies, it will be used the paired Student *t*-test or Wilcoxon tests as appropriate. Comparisons between groups will be performed using Student *t* test or Mann–Whitney U according to the distribution. All tests will be 2 tailed, and p values of less than 0.05 will be assumed to represent statistical significance. All analyses will be performed using SPSS ver. 16.0.

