**Methods/design:**

50 patients with CP, both gender, aged between 19 and 60 years will be enrolled in this study. The inclusion criteria are: voluntary participation, patient with hemiparesis, quadriparesis or diparetic CP, with ability to understand and respond to verbal commands. The exclusion criteria are: patients undergoing/underwent orthodontic, functional maxillary orthopedic or botulinum toxin treatment. Polysomnographic and surface electromyographic exams on masseter, temporalis and suprahyoid will be carry out in all sample. Questionnaire assessing oral characteristics will be applied. The sample will be divided into 5 treatment groups: Group 1: neuromuscular electrical stimulation; Group 2: laser therapy; Group 3: LED therapy; Group 4: neuromuscular electrical stimulation and laser therapy and Group 5: neuromuscular electrical stimulation and LED therapy. All patients will be treated during 8 consecutive weeks. After treatment, polysomnographic and electromiographic exams will be collected again.

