## Aims and hypotheses

This study aims to assess the sleep variables and masticatory dynamics by means of PSG and EMG, respectively, prior and after neuromuscular electrical stimulation, associated or not with low power laser irradiation (Gallium Arsenide- Aluminun, = 780 nm) and LED (= 660 nm) in patients with cerebral palsy. It is expected that Laser e LED biostimulation will promote the morphophysiologic recovering of muscle fibers and the decreasing of inflammatory process that will be observed through the achievement of muscular physiology within normal patterns established in this study. It is hypothesized that oxyhemoglobin desaturation, caused by pauses in breathing during sleep, can lead to harmful function in neuromuscular system in individuals with CP. We also hypothesize that electrical stimulation, led therapy and laser therapy will contribute to balance the muscular function, adjusting to physiologic patterns of muscular activity, in rest and isometric positions 
[17,18]. The sample will be divided according the randomization rules, in 5 groups with 10 patients (G1,G2,G3,G4,G5). In the G1 will be applied the electrical stimulation, in the G2 laser therapy, in the G3 led therapy, in the G4 the association of led therapy and electrical stimulation and in the G5 the association of laser therapy and electrical stimulation.

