## Discussion

This study will evaluate the effects of lower power laser, neuromuscular electrical stimulation, LED therapy, as well as neuromuscular electrical stimulation plus LED therapy and neuromuscular electrical stimulation plus laser therapy on the masticatory muscles activity in adults with CP, by means of surface electromyography. We believe that electrical stimulation may act in the modulation of muscle hyperactivity/hypoactivity, adjusting them to a level close to normality. Also, we expect the LED and laser morphophysiological favor recovery, which will be observed clinically by the absence or reduction of pain. In addition, polysomnography will be used to evaluate the sleep variables and to detect sleep-breathing disorders, and we believe that the sleep quality will be improved after therapies application.

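### With all five arms active, the planned paired before/after tests cannot support effectiveness conclusions, and for rest and isometric EMG the mean signed change may not measure the hypothesised normalisation

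*Protocol article*

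**What the plan says.** The Statistical analysis section of the Protocol article gives two families of tests. For values before and after therapy, "it will be used the paired Student *t*-test or Wilcoxon tests as appropriate". Then: "Comparisons between groups will be performed using Student *t* test or Mann–Whitney U according to the distribution". Both use two-sided p < 0.05, and neither is named as the basis for conclusions.

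Other sections pull in different directions. Phases of electromyographic exam says "Data obtained will be compared among each group to verify the effectiveness of the proposed therapies", which points toward comparison between arms, though the wording is ambiguous. Aims and hypotheses is framed within patients: the study will "assess the sleep variables and masticatory dynamics by means of PSG and EMG, respectively, prior and after neuromuscular electrical stimulation". The Discussion is framed the same way for sleep: "we believe that the sleep quality will be improved after therapies application".

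The abstract lists the arms as "Group 1: neuromuscular electrical stimulation; Group 2: laser therapy; Group 3: LED therapy; Group 4: neuromuscular electrical stimulation and laser therapy and Group 5" (stimulation with LED). Every arm receives active treatment for eight weeks.

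On muscle activity, the Discussion expects that "electrical stimulation may act in the modulation of muscle hyperactivity/hypoactivity, adjusting them to a level close to normality". Aims and hypotheses states a similar expectation for stimulation, LED and laser, in rest and isometric positions, and expects laser and LED to bring "muscular physiology within normal patterns established in this study". The EMG summary is average RMS (Analysis of sEMG data).

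**The concern.** There are two separate problems.

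**No untreated comparison.** A paired test inside an arm asks whether the mean changed, not whether the therapy changed it. Polysomnography is one night before and one night after treatment. EMG, bite force and opening are recorded three times per appointment over four phases. Familiarity with the laboratory and practice with the tasks could therefore move values without any treatment effect. The before/after aim and sleep expectation can be addressed only by the paired tests, and the text does not acknowledge that limit. An arm with p < 0.05 could be reported as an effective therapy.

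**Signed mean against a normalisation hypothesis.** If normalisation means a fall in overactive muscles and a rise in underactive ones, mean signed RMS change is not a measure of it. Real normalisation could go undetected. The between-group tests do not cure this, because signed RMS change can cancel there too.

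**Working it through.** **Inputs from the Protocol article.** Five active arms (abstract; Aims and hypotheses). Ten patients per arm, 90% power, alpha 0.05 (Sample size). Two-sided p < 0.05 (Statistical analysis).

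**Assumed inputs, not in the document.** The size of any shift unrelated to treatment, and the mix of patients above and below normal. Both are shown as ranges.

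**1. The plan's own figure.** The 90% power cannot be reproduced, because no test, outcome, effect size or SD is given. Solving backwards for n = 10, two-sided:
- Paired t (9 df, critical value 2.262): power = P(|T| > 2.262) with noncentrality dz × √10. This reaches 90% at dz = 1.15 (more exactly 1.155; 1.155 × 3.162 = 3.65).
- Two-sample t (18 df): 90% at d = 1.53.

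**2. Paired test with no treatment effect and a shared shift m (in SDs of change).** Noncentrality is m√10. For any of five independent arms, on one outcome, the probability is 1 − (1 − p)^5.

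| m | m√10 | One arm significant | At least one of five |
|---|---|---|---|
| 0 | 0 | 5% | 23% |
| 0.1 | 0.32 | 6% | 26% |
| 0.3 | 0.95 | 14% | 52% |
| 0.5 | 1.58 | 29% | 82% |
| 0.8 | 2.53 | 62% | 99% |

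Example: 1 − (1 − 0.293)^5 = 1 − 0.177 = 0.82. The first row is ordinary multiplicity (1 − 0.95^5) and is not part of this point.

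**3. The same shift between arms.** A shift common to both arms drops out of their difference. In simulation with m = 0.8 in each arm, a two-sample t-test of change was significant about 5% of the time.

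**4. Cancellation, for rest and isometric EMG only.** Suppose every patient moves D = 1.155 SD toward normal and a share q moves in the opposite direction to the rest. If each patient's direction is random, mean change is (1 − 2q)D and its SD is √(1 + 4q(1 − q)D²).
- q = 0.2: 0.693 / 1.361 = 0.51
- q = 0.3: 0.462 / 1.456 = 0.32
- q = 0.5: 0

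Simulated paired t power, n = 10:

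| Moving one way | Direction random per patient | Exact split in the arm |
|---|---|---|
| 100% | 90% | 90% |
| 80% | 33% | 23% |
| 70% | 17% | 6% |
| 50% | 5% | 0.3% |

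The random column applies if the share describes the patient population. The exact-split column applies if each arm holds precisely 8:2, 7:3 or 5:5. A test on movement toward normal keeps about 90% power whatever the mix.

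**The case against.** - **Between-arm tests are already planned.** A reader might infer that effectiveness is judged only from the paired tests. The documents do not support that. The next sentence of Statistical analysis plans group comparisons, and Phases of electromyographic exam links effectiveness to comparing the data among groups. Listing the paired tests first is sentence order, not a hierarchy. What stands is that no sentence says which family decides, and the aim and sleep expectation are before/after claims.
- **Misreading across arms is speculative.** Direct group tests are the usual safeguard against comparing p values between arms, and they are in the plan. This stands.
- **Opposite signs between patients are not stated.** Muscles could be too active at rest and too weak in isometric contraction. Channels and positions are recorded separately, so tests by muscle and position would then not cancel. This stands: cancellation is conditional on the same muscle in the same task being above normal in some patients and below in others. Sleep and pain are given one direction, and nothing extends the argument to bite force or mouth opening.
- **The sizes rest on assumed inputs.** Also true. At a 0.1 SD shift the any-arm figure (26%) is barely above the 23% from multiplicity alone. Regression to the mean is the weakest of the three mechanisms here, since eligibility does not select on EMG or sleep values.
- **The normal patterns may be adopted rather than derived.** A reader might infer that the trial cannot have normal values because every participant has cerebral palsy. The phrase may instead mean reference patterns adopted for the study, defined in a fuller document. The source is unclear, not shown to be impossible.

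**Conclusion.** The point holds in a limited form and should be acted on. Because all five arms are treated, the within-arm tests cannot support a claim that any single therapy works, and the plan leaves room for such a claim. The chance of at least one spuriously significant arm runs from 26% to 99% over shared shifts of 0.1 to 0.8 SD. That range depends wholly on the assumed shift, for one outcome and a t-test. The randomised between-arm tests are protected from a shift common to all arms, but they estimate only relative or add-on effects.

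For EMG amplitude at rest and in isometric position, mean signed RMS can miss real normalisation if the direction of abnormality differs between patients. Power then falls from 90% to between 33% and 5% with random directions, or between 23% and 0.3% with exact splits. The document does not give the mix, so this is a risk and not a demonstrated loss.

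**What to change.** 1. In Statistical analysis, state that effectiveness conclusions rest on randomised between-arm comparisons of change. Examples are stimulation added to light, (G4+G5) v (G2+G3), and light added to stimulation, (G4+G5) v G1, keeping the laser v LED comparison. The pooled contrasts are unaffected by the G4 and G5 labels being exchanged between the abstract and Aims and hypotheses; a laser v LED comparison that uses those two arms needs the labels reconciled. The first contrast is 20 v 20, with 90% power at 1.05 SD, against 1.53 SD for 10 v 10.
2. Report within-arm changes descriptively with 95% confidence intervals, and state that no arm estimates an effect against no treatment.
3. For rest and isometric EMG, add a between-arm analysis of absolute distance from a reference value fixed before the data are analysed, adjusted for baseline. It should be between arms because distance from a reference is itself open to retest effects and regression to the mean.
4. In Aims and hypotheses, say where the normal patterns come from, since no participant without cerebral palsy is enrolled.

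The cost is wording and analysis only, with no added arm or visit. The downsides are that absolute claims for a single therapy can no longer be made, and that a reference value must be chosen and justified.

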## Discussion

This study will evaluate the effects of lower power laser, neuromuscular electrical stimulation, LED therapy, as well as neuromuscular electrical stimulation plus LED therapy and neuromuscular electrical stimulation plus laser therapy on the masticatory muscles activity in adults with CP, by means of surface electromyography. We believe that electrical stimulation may act in the modulation of muscle hyperactivity/hypoactivity, adjusting them to a level close to normality. Also, we expect the LED and laser morphophysiological favor recovery, which will be observed clinically by the absence or reduction of pain. In addition, polysomnography will be used to evaluate the sleep variables and to detect sleep-breathing disorders, and we believe that the sleep quality will be improved after therapies application.
